#### Statistical procedure

The statistical procedure for the selected, confirmatory analyses will follow the sequentially rejective multiple testing approach described by Bretz et al. [42]. The two primary endpoints (LEP N2-P2 amplitude change at non-sensitized arm and PEP N2-P2 amplitude change at sensitized arm) will be tested for their differences between the treatment arms tapentadol versus placebo, first. This will be conducted in parallel, splitting the overall *α* equally between the two endpoint tests, i.e., each test has a type I error of *α*/2. If any of these two tests shows significant differences, key secondary analyses will be conducted using the *α*-levels as passed on from initial/prior tests according to specified weights. The exact procedure (with the local levels as well as the weights with which to pass *α*-levels on) is shown in Fig. 5, and related specifications are provided in the subsequent subsections.

**Fig. 5 Fig5:**
[figure not shown]
Statistical procedure. The sequentially rejective multiple testing approach used for the selected confirmatory analyses. The two primary endpoints (LEP N2-P2 and PEP-N2-P2) will be tested in parallel, splitting the overall *α* equally between the endpoint tests. If any of these two tests shows significant differences, key secondary tests will be conducted using the *α*-levels as passed on from initial/prior tests according to specified weights

#### Primary analysis of primary endpoints

The primary analyses consist of two parallel tests (based on full analysis set data) which differ exclusively in the endpoint LEP N2-P2 endpoint and PEP N2-P2 endpoint). Only the analysis for the LEP N2-P2 change endpoint is specified here. Analysis of the PEP N2-P2 change endpoint is identical and will be provided in the statistical analysis plan.

LEP N2-P2 change endpoint data being repeated measurements (at the T + 60 min time-point post-dose) across the four periods will be analyzed with a mixed effect model with treatment (4 levels), period (4 levels), center, and sequence as fixed effects. The variance-covariance structure for the repeated measure variable period should be chosen as CS (compound symmetry).

The LS means difference of treatment tapentadol versus placebo will be estimated and tested based on this model and the estimate as well as the corresponding unadjusted confidence interval and *p* value will be provided.

If either (or both) of the primary endpoints’ tests show significant differences between tapentadol and placebo in the sense that the *p* value is below the corresponding local alpha level, the differences are confirmed, and the testing procedure continues according to the graph above.

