### Sample size {14}

Given the rationale of improving preclinical to clinical translation of pain effects and the intention to use these biomarkers in future early clinical pharmacology studies, a robust signal in a small number of subjects is required if this biomarker is to prove useful in early drug development. In fact, if the investigated drugs and measured effects do not show robust (i.e., significant primary) biomarker signals on the basis of several tens of subjects, the overall usefulness of this biomarker is rather limited. Therefore, the following illustration of the estimated power of this study with a range of 10 to 30 subjects (in total) should serve as justification for the (evaluable) sample size to be chosen at 12 overall (preferably at one center with additional centers providing data for reliability testing at similar sample sizes).

Knowledge on the variability and effect sizes of EEG parameters are available with tramadol versus placebo as treatment in healthy subjects [27], with alfentanil versus baseline in healthy subjects [26], as well as before versus after morphine treatment in chronic pain patients [32]. The study by Truini et al. [27] conveys effects (i.e., group differences of the LEP N2-P2 changes relative to baseline) around 60% (placebo group) and 90% (tramadol group), i.e., a 30% group difference. The provided data by Petersen-Felix et al. [26] suggests standard deviation (SD) parameters for LEP peak-to-peak amplitude of the negative-positive vertex to be around 25%. With the tapentadol versus placebo comparison of the primary analysis (on LEP peak-to-peak amplitude relative changes from baseline, 2-sided type I error of *α*/2 = 0.025) being essentially a paired *t* test with assumed correlation of 0.3, the power graph shown in Fig. 3 yields 12 evaluable subjects in total to be a reasonable sample size for at least 85% power. While this appears sufficient for the primary analysis, data for similar numbers of subjects would be recommended from all centers for test-retest reliability investigations. Therefore, sample sizes of 8 to 12 subjects treated for all four study periods are required in each participating center.

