#### Definition of the primary endpoints

The first primary endpoint is the percentage of change in amplitude of the negative-positive vertex potential (N2-P2 complex) of LEPs at time-point T + 60 min post-drug administration vs. the pre-drug time-point, at the non-sensitized arm. The second primary endpoint is the percentage of change in amplitude of the N2-P2 complex of PEPs at time-point T + 60 min post-drug administration vs. the pre-drug time-point, at the sensitized arm.
$$ \mathrm{endpoint}=\frac{\mathrm{N}2-\mathrm{P}{2}_{\mathrm{amp}}\left(+60\ \min \right)-\mathrm{N}2-\mathrm{P}{2}_{\mathrm{amp}}\left(\mathrm{baseline}\right)}{\mathrm{N}2-\mathrm{P}{2}_{\mathrm{amp}}\left(\mathrm{baseline}\right)} $$

The primary analysis of the two primary endpoints will focus on the comparison of the tapentadol vs. placebo effects.

Within the error-controlled testing procedure, both primary endpoints will also be tested in key secondary analyses comparing lacosamide vs. placebo and pregabalin vs. placebo effects. Also within the error-controlled testing procedure, the key secondary analyses will also compare a third endpoint: the percentage of change in amplitude of ongoing theta band EEG oscillations at time-point T + 60 min post-drug administration vs. the pre-drug time-point.
$$ \mathrm{endpoint}=\frac{{\mathrm{theta}}_{\mathrm{amp}}\left(+60\min \right)-{\mathrm{theta}}_{\mathrm{amp}}\left(\mathrm{baseline}\right)}{{\mathrm{theta}}_{\mathrm{amp}}\left(\mathrm{baseline}\right)} $$

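### Percentage change is analysed without a baseline covariate: the planned test is valid but gives up precision, which matters mainly for effects smaller than the planned LEP effect

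*Protocol article*

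**What the plan says.** The protocol article, under Definition of the primary endpoints, states: "The first primary endpoint is the percentage of change in amplitude of the negative-positive vertex potential (N2-P2 complex) of LEPs" at 60 minutes against the pre-drug value of the same period. The formula is (post − baseline)/baseline. PEP at the sensitized arm and theta amplitude are defined in the same way.

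Under Primary analysis of primary endpoints, the LEP data "will be analyzed with a mixed effect model with treatment (4 levels), period (4 levels), center, and sequence as fixed effects". For the covariance, "The variance-covariance structure for the repeated measure variable period should be chosen as CS (compound symmetry"). For the second primary endpoint, "Analysis of the PEP N2-P2 change endpoint is identical and will be provided in the statistical analysis plan". Key secondary analyses of primary endpoints carries the model to pregabalin, lacosamide and theta.

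No baseline covariate and no transformation is named. The only mention of covariance models is under Analysis of test-retest reliability, and it concerns reliability alone.

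**The concern.** In a crossover each subject already serves as their own control. Dividing by a separate pre-dose value in each period adds that value's measurement error to every treatment contrast. A covariate would use the baseline only as far as it predicts the post-dose value; a change score imposes a fixed weight.

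The Sample size section argues that a biomarker is useful only if it shows a robust signal in few subjects, and that a non-significant result is informative in itself. A null result caused partly by an inefficient analysis would then count against the biomarker.

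**Working it through.** **The plan's own figure.** The inputs come from the Sample size section: "i.e., a 30% group difference"; an SD "for LEP peak-to-peak amplitude of the negative-positive vertex to be around 25" percent; correlation 0.3 between periods; "2-sided type I error of *α*/2 = 0.025".

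- SD of the paired difference: 25 × √(2 × (1 − 0.3)) = 29.58. Standardized effect: 30/29.58 = 1.014.
- Exact paired t test, 12 pairs: power 80.5%, against the stated figure of at least 85%. The normal approximation gives 89.8%, and the larger residual degrees of freedom of a four-period model give about 87%. The power graph is not shown, so the variant used cannot be confirmed. This gap is a separate matter; 80.5% serves here as the starting value.

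**Effect of the covariate.** Let σ² be the within-subject, period-level variance of the amplitude, taken as equal before and after dosing on an additive or log scale. Let rho be the correlation of the two at that level.

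- Change score, contrast of two periods: 2 × 2σ²(1 − rho) = 4σ²(1 − rho).
- Baseline-adjusted: 2σ²(1 − rho²).
- Ratio: (1 − rho²)/(2(1 − rho)) = (1 + rho)/2.

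The ratio is below 1 unless rho = 1. The protocol does not give rho. The 0.3 above is the correlation of the change endpoint between periods, which is a different quantity, so rho is shown as a range.

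Power in percent, multiplying 29.58 by √((1+rho)/2) and spending one degree of freedom. For example, at rho 0.5 the SD is 29.58 × √0.75 = 25.62. The 15-point effect is an assumption.

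| Evaluable N, effect | Planned | rho 0 | 0.3 | 0.5 | 0.7 | 0.9 |
|---|---|---|---|---|---|---|
| 12, 30 points | 80.5 | 98.0 | 93.8 | 90.0 | 85.8 | 81.5 |
| 32, 30 points | 99.9 | >99.9 | >99.9 | >99.9 | >99.9 | >99.9 |
| 32, 15 points | 69.5 | 95.0 | 87.8 | 82.4 | 77.0 | 71.8 |
| 48, 15 points | 88.0 | 99.5 | 97.7 | 95.6 | 92.8 | 89.7 |

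The 32 and 48 are four centers times 8 or 12 evaluable subjects (Study setting; Sample size).

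**Simulation including the log scale.** A four-period Williams crossover was simulated with assumed log-scale SDs: subject 0.35, day 0.15, residual 0.20. Here rho = 0.15²/(0.15² + 0.20²) = 0.36. Alpha was 0.025.

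| Setting | Percentage change | Same, plus period baseline | Log amplitude plus log baseline |
|---|---|---|---|
| n = 12, 30% reduction | 68% | 81% | 91% |
| n = 48, 15% reduction | 66% | 81% | 87% |

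The gain of 23 points at n = 12 thus splits into about 13 from the covariate and 10 from the log scale. With residual SD 0.15 (rho 0.50), power at n = 12 goes from 92% to 99%.

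With day SD 0.40 and residual SD 0.20, rho = 0.16/(0.16 + 0.04) = 0.80 and the gains shrink. At n = 12 power goes from 66% to 80%, with 77% reached by log change alone. At n = 48 with a 15% reduction it goes from 64% to 74%. Type I error was 2–3% for all analyses under the 0.15/0.20 SDs.

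**The case against.** The strongest reply is that nothing here is an error. Endpoint, model and sample size share one scale, type I error holds, and percentage change is a readable quantity for a biomarker. All of that stands.

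The reply on sample size also stands for LEP under tapentadol. The analysis uses the full analysis set from four centers, not 12 subjects. With the planned inputs, power is 99.9% or more at 32 to 48. In the simulation with residual SD 0.20 and a 30% reduction, the planned analysis already reaches 98.8% at n = 32. It does not settle the co-primary PEP, theta or the other drugs.

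The size of the gain rests on an unstated correlation, and each baseline averages 30 stimuli per forearm, which limits the noise. This is why only a range can be given. The simulated model also implies no correlation of change scores between periods, whereas the plan assumes 0.3, so it is illustrative rather than calibrated to the plan.

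The article leaves final detail to the statistical analysis plan. But it states the endpoint formula and the model terms outright, so the choice can be reviewed as it stands.

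**Conclusion.** The concern holds as a point of efficiency. The stated model leaves out a baseline that the trial collects in every period, and under the equal-variance model the adjusted contrast is more precise for any rho below 1, apart from the degrees of freedom spent. At n = 12 with a 30% reduction the gain runs from about 1 point (rho 0.9, covariate alone, plan's inputs) to more than 20 points (rho 0.36, covariate and log scale, assumed SDs). For LEP with the planned effect at the planned total size it is negligible. For an assumed 15-point effect at 32 subjects, the covariate alone adds from about 2 points (rho 0.9) to 25 (rho 0).

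A reader might infer more than the documents support:

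- That the planned test is invalid. It is not; its type I error stays near nominal.
- That compound symmetry fails, or that one low baseline will dominate the estimate. Both are possible for a ratio, but the document holds no data that show either.
- That the gain is free. It is not, as set out with the fix.

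**What to change.** Before unblinding, for LEP, PEP and theta amplitude, add two covariates to the stated mixed model: the period's pre-dose amplitude and the subject's mean pre-dose amplitude across periods. Both are needed, because one pooled slope mixes within- and between-subject effects and loses part of the gain (78% against 88% power in one simulated case: rho 0, within-subject SD 0.2, n = 12).

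Preferably take log amplitude at 60 minutes as the outcome with log baselines. Back-transform the treatment difference to a percentage reduction versus placebo with its confidence interval. Keep the raw percentage-change analysis as supportive.

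The cost is one or two degrees of freedom and no new data. On the log scale the estimate becomes a ratio of geometric means, amplitudes must be strictly positive, and the endpoint wording and sample-size basis must be restated. The closing paragraph of Analysis of test-retest reliability calls for a protocol amendment if the study is still ongoing, as well as a change to the statistical analysis plan.

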#### Key secondary analyses of primary endpoints

These statistical analyses are considered confirmatory only provided they have received local *α*-levels (type I error greater than 0) from prior tests rejecting their corresponding null hypotheses.

The method for testing the primary endpoints comparing the other treatment groups versus placebo mirrors the model specifications of the primary analysis above but using the Dunnett-adjusted estimation and testing results to compare pregabalin and lacosamide with placebo respectively.

The method for testing the key secondary endpoint theta band oscillations (theta_amp_) in ongoing EEG is similar to these specifications using the model of the primary analysis above but extending the Dunnett comparisons to all three drug treatment arms versus placebo.

#### Analysis of secondary endpoints

All secondary endpoints will be compared across the four treatment groups using the same approach as the analysis of the primary endpoints. These analyses, even if using the general significance level above, are considered exploratory.

### Interim analyses {21b}

No interim analysis is foreseen for this study. Should it later become necessary to conduct an interim analysis, it will be described in an amendment to this protocol prior to conduct of the analyses. The amendments will include considerations on maintaining the blind as well as specifications of appropriate statistical adjustments for unplanned interim analyses.

### Methods for additional analyses (e.g., subgroup analyses) {20b}

There are many other analyses corresponding to the additional time-points when assessments are done (180 and 360 min post-dose), but also by the collection of other biomarkers, i.e., other outcomes. A selection of these is briefly described below.
Latency of the N2 and P2 components of LEPs and PEPs. In addition to affecting the amplitude of the N2-P2 complex of LEPs and PEPs, the different drugs could also affect the latency of laser- and/or pinprick-evoked brain responses, via effects on peripheral and/or central conduction times. We will thus examine whether the latencies of the N2 and P2 components of LEPs and PEPs are sensitive to drug effects.Early-latency N1 component of LEPs. In addition to the N2-P2 complex, laser stimuli also elicit an early-latency negative wave, referred to as the N1 component, and maximal at central-temporal electrodes contralateral to the stimulated upper limb. This component is thought to reflect earlier stages of nociceptive processing, primarily originating from the contralateral operculo-insular cortex and/or the primary somatosensory cortex. We will thus examine whether the amplitude and/or latency of this N1 component is sensitive to drug effects.Dimensionality reduction and feature selection methods. Spatio-temporal or spatio-spectral blind source separation techniques such as independent component analysis [43], microstate EEG analysis [44], or extensions of this analysis technique currently developed by UCLouvain can be used to reduce the dimensionality of multichannel ongoing EEG as well as pain-evoked brain responses to identify EEG features that may be sensitive to drug effect on nociception and/or its interaction with sensitization.Single-trial ERP amplitude/latency dispersion measures. Single-trial estimates of the amplitude of LEP N2-P2 amplitude and PEP N2-P2 amplitude can be obtained using methods developed in part by UCLouvain [45]. These estimates can be used to examine whether drug administration affects the trial-to-trial variability in ERP amplitude or latency.Cluster-based point-by-point LEP and PEP waveform analysis. Rather than restricting the analysis of LEP and PEP waveforms to the estimation of amplitude and latency of N2 and P2 peaks, a point-by-point waveform analysis can be used to compare the entire waveform of LEPs and PEPs across conditions. This approach, combined with cluster-based permutation testing to address the issue of multiple comparisons, has been used successfully to identify changes in PEPs induced by HFS [5, 46].Topographical analysis of LEPs and PEPs, and source waveform estimation for primary and secondary somatosensory cortex, insula, anterior cingulate cortex, and prefrontal cortex activation. Because the different drugs may differentially affect the different cortical sources of LEPs and PEPs, the topographical distribution of the N1, N2, and P2 components of PEPs and of the N2 and P2 components of PEPs will be compared across the different treatment groups. Furthermore, source waveform estimation of laser- and pinprick-evoked activity in the primary and secondary somatosensory cortex, the insula, the anterior cingulate cortex, and the prefrontal cortex can be obtained using distributed source modeling (e.g., sLORETA algorithm) [47]. This can be used to assess selective changes in the magnitude of the activity generated within these different structures.Ongoing EEG oscillations. In addition to drug effect on the magnitude of theta band EEG oscillations, we will also assess potential drug effects on delta-, alpha-, beta-, and gamma-band oscillations, as these could be differentially modulated by the different treatments. This will include analysis of cross-frequency coupling, and analysis of across-channel phase coherence. Furthermore, previous studies have shown that both laser stimuli and pinprick stimuli induce transient increases and decreases in the magnitude of these ongoing EEG oscillations, referred to as event-related synchronization (ERS) and desynchronization (ERD) [5, 36, 48]. Therefore, we will examine whether the different treatments affect laser- and pinprick-induced ERD and ERS.

#### Pharmacometric analyses

The data collected in this trial together with the data from the other three IMI2-PainCare-BioPain-RCTs and the preclinical studies of the BioPain project will be subject to pharmacometric analyses with the intention to validate biomarkers that can translate from preclinical to clinical readouts. As both drug concentrations and biomarker responses are measured at several time-points post-drug administration, the relationship between drug levels and select biomarkers will be explored and modeled. The pharmacometric analysis will be described in a separate pharmacometric analysis plan and will consist briefly in developing population pharmacokinetic/pharmacokinetic (PK/PD) models estimating the primary PK parameters (i.e., apparent volume of distribution, and total plasma clearance), the primary PD parameters (i.e., C50, the plasma or effect site concentration that elicits a response equal to half of the maximum attainable effect (EMAX)), and their associated inter-individual variability.

#### Analysis of demographic data and other baseline characteristics

Analyses of demographic data and other baseline characteristics will consist of descriptive summary statistics. While these tables may provide the summaries by groups (i.e., treatment sequences), there will be no statistical tests conducted on baseline characteristics differences. Data will also be listed. Details will be provided in the statistical analysis plan.

#### Analysis of test-retest reliability

A reliability analysis will investigate the biomarker and their measurement characteristics using the following concepts, all based on the full analysis set. Detailed specifications will be provided in the statistical analysis plan. Assessment of the repeatability of a (individual) biomarker response measurement method will use the statistics described by Bland and Altman [49] (such as differences against means plots). Also, within- and between-subject variabilities will be estimated using the mixed AN(C) OVA models including the corresponding variance components according to the repeated measurements design. These include data across time-points within a “visit” (e.g., during placebo treatment period) or across “visits” (e.g., baseline measurements across the treatments periods) as applicable. Should measurement methods of the same biomarker be compared, the agreement statistics of Bland and Altman will be used. Assessment of the reproducibility will follow the statistics (such as difference limits, minimum significant difference, limits of agreement) as described in standard guidance documents. As applicable, further statistics presented for test-retest characteristics may include correlations (such as concordance correlation coefficients, intraclass correlation coefficients), coefficients of variations, and sensitivity to change statistics, e.g., smallest real difference [50].

Any changes to the planned statistical analyses, if considered prior to unblinding, will be described and justified in an amendment to the protocol (if study is still ongoing) and to the statistical analysis plan. Deviations from planned analyses will also be explained in the final study report.

### Methods in analysis to handle protocol non-adherence and any statistical methods to handle missing data {20c}

The analysis method of the mixed effect model already takes missing data into account and missing data issues are also partly addressed by the sensitivity analyses. More thorough and complete descriptions of missing data handling will be provided in the statistical analysis plan.

### Plans to give access to the full protocol, participant level-data, and statistical code {31c}

This will be determined at the end of the project period of IMI-PainCare.

